#### Secondary outcome variables

There will be 7 secondary outcomes for this trial: (1) gait speed, (2) two-minute walk distance, (3) functional status, (4) balance confidence, (5) patient quality of life, (6) health service utilization and (7) caregiver burden.

### Gait speed

Gait speed is related to the severity of impairment in the home and the community and has been used in many studies [21]. Gait speed will be measured using the timed 5-meter walk test. The individual walks without assistance for 5 meters (16.4 feet) and the time is measured for the intermediate 3 meters (9.8 feet) to allow for acceleration and deceleration. Timing is started when the toes of the leading foot crosses the 1-meter mark and it is stopped when the toes of the leading foot crosses the 4-meter mark. Assistive devices can be used but would be kept consistent and documented from test to test. Three trials are done and the average will be recorded for each session. The participant will be assessed when they are walking at normal comfortable speed and at maximum speed.

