#### Inclusion criteria

The inclusion criteria for the trial are as follows: (1) age ≥ 40 years, (2) recent stroke (defined as stroke diagnosis occurring within 4 weeks prior to admission into inpatient rehabilitation unit or hospital), (3) able to sit unsupported for 30 s, (4) able to stand on the non-paretic leg for >4 s, (5) able to walk at least 2 m with maximum of 1 person assisting, (6) able to follow a 2-step command, (7) living in the community before stroke and expected to be discharged home, (8) has a caregiver when the patient is doing the exercises for safety reasons, as the tele-therapist is not present when the patient is doing the exercise and a caregiver is needed to catch the patient if he/she should fall.

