### 2-minute walk distance

In addition to the gait speed, the distance a person can walk and the amount of daily walking that a person is able and willing to do are strong indicators of his or her health and condition [21]. Hence, the two-minute walk test will also be conducted. Individuals walk at their usual speed as far as they can without assistance for 2 min and the distance is measured. Assistive devices can be used but would be kept consistent and will be documented from test to test.

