#### Analysis for outcome measures

Data entered will be checked for accuracy at least twice by at least two independent assessors. To understand the structure of missing data and to reduce bias from uncertainty of missing data, multiple imputations will be performed using the Markov Chain Monte Carlo method. All scale-based measures used in this study will be screened via an internal consistency test (Cronbach’s alpha test) before creating a summative score. Furthermore, rigorous validity tests will be performed in two ways: person-centered tests (latent class analysis) and variable-centered tests (exploratory and confirmatory factor analyses).

For descriptive statistics, independent two-sample *t*-test and Analysis of Covariance (ANCOVA) will be performed on all continuous outcome measures (i.e. Shah-modified BI, ABC Scale, gait speed, two-minute walk test and ZBI) between tele-rehabilitation vs. usual care group if outcomes are normally distributed. Mann–Whitney *U* test will be performed on data with skewed distribution to test differences between treatment groups. Chi-square test will be performed on categorical variables. Confounders are age, gender, ethnicity and marital status. Multiple linear regressions will be used to adjust for differences in confounders between intervention and control groups for continuous outcome variables. Ordered logistic regressions will be used to adjust for differences between intervention and control groups for continuous categorical variables. For these multivariate linear and logistic regressions, we will use survey analysis processes with robust standard errors which accounts for nesting effects within patient data as a result of clustering by different recruitment centers. For all statistical analyses, the level of significance (α) will be taken at 0.05. Analyses will be based on the intention-to-treat approach. We will use STATA version 12 for statistical analysis and significance level is set at P < 0.05.

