### Cost-effectiveness

Cost effectiveness analyses from both the health system perspective will be performed using the standard quality of life measure EQ-5D and measures of health service utilization and cost over the study period. Quality adjusted life years (QALYs) will be computed for each individual using the EQ-5D score. Incremental cost-effectiveness ratio (ICER) will subsequently be computed to assess incremental costs per QALY gained between treatment and control group. To determine confidence intervals for ICER, a non-parametric bootstrapping method with 1000 replications of the data will be performed. When dominance is observed, full cost analyses will be conducted to determine mean savings per patient.

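### Both walking tests require unassisted walking, but entry admits people who need a helper, and the only missing-data rule is blanket multiple imputation: inability to walk could be replaced by a walker's speed

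*Protocol article*

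**What the plan says.** All references are to the protocol article.

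- **Inclusion criteria:** a participant must be "able to walk at least 2 m with maximum of 1 person assisting".
- **Gait speed:** "The individual walks without assistance for 5 meters", timed over the middle 3 m. Assistive devices are allowed.
- **2-minute walk distance:** "Individuals walk at their usual speed as far as they can without assistance for 2 min". Devices are again allowed.
- **Secondary outcome variables:** the two tests head the list. "There will be 7 secondary outcomes for this trial: (1) gait speed, (2) two-minute walk distance".
- **Analysis for outcome measures:** for missing data, "multiple imputations will be performed using the Markov Chain Monte Carlo method". The same section says "Analyses will be based on the intention-to-treat approach". For skewed outcomes it provides a Mann–Whitney test: this "test will be performed on data with skewed distribution to test differences between treatment groups".
- **Cost-effectiveness:** "Quality adjusted life years (QALYs) will be computed for each individual using the EQ-5D score".

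Neither test description says what is recorded when a participant cannot do the test. The analysis section does not separate a result that was not collected from one that could not exist.

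**The concern.** The trial deliberately enrols people who may need a helper to walk, then measures two of its seven secondary outcomes with tests that forbid a helper. Some will have regained independent walking by 3 or 6 months and some may not. For those who have not, the timed gait test produces no time. Unless a score is assigned, that cell is empty, and the only stated treatment of an empty cell is imputation.

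Inability to walk alone is the worst result on the scale, not an ordinary speed that nobody recorded. A missing-at-random model fitted to people who can walk fills the cell with a speed typical of walkers, or at best of slow walkers. Regaining independent walking is one of the gains this programme might produce, since it trains leg strength, standing balance and walking. That gain could therefore be reduced or lost in the gait-speed comparison. People who have only just become able to walk also enter the observed data as slow walkers and lower their own arm's mean.

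**Working it through.** The article gives no expected gait speed, standard deviation or share unable to walk, so there is no figure of the plan's to reproduce. Everything below is illustrative.

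**Assumed inputs.** Walking ability is normal with mean 0.6 m/s and SD 0.3 m/s. A participant cannot do the test if below a threshold that excludes 10% or 25% of controls. There are 50 per arm, the planned number.

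**Identity.** Let p be the share unable and m the mean speed of those able, with C for control and T for tele-rehabilitation.

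- Inability scored 0: difference = (1 − p_T)·m_T − (1 − p_C)·m_C.
- Inability imputed from walkers in the same arm: difference ≈ m_T − m_C.

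The two agree when p and m are equal in the arms and generally part otherwise.

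**Worked case: benefit only near the threshold.** Suppose 25% of controls are unable. Half of the corresponding treated patients become slow walkers, at 0.02 to 0.12 m/s above the threshold, and nobody else changes.

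- Threshold = 0.6 − 0.3 × 0.6745 = 0.398 m/s.
- m_C = 0.6 + 0.3 × 0.3178/0.75 = 0.727.
- Mean speed of the newly able = 0.398 + 0.07 = 0.468.
- m_T = (0.75 × 0.727 + 0.125 × 0.468)/0.875 = 0.690.
- Scored 0: 0.875 × 0.690 − 0.75 × 0.727 = +0.058 to +0.059 m/s, allowing for rounding.
- Imputed within arm: 0.690 − 0.727 = −0.037 m/s.

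**Simulation.** 1,500 trials per scenario, normal-model multiple imputation with 10 imputations, using arm alone or arm plus a correlate of walking ability (r = 0.6 or 0.8). Entries are tele-rehabilitation minus control in m/s. Ranges in the third column are run-to-run variation.

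| Scenario | Unable, control / treated | Scored 0 | Imputed: arm only | with r 0.6 | with r 0.8 |
|---|---|---|---|---|---|
| No effect | 10% / 10% and 25% / 25% | about 0 | about 0 | about 0 | about 0 |
| Uniform +0.1 | 10% / 5% | +0.101 to +0.104 | +0.075 | +0.083 | +0.091 |
| Uniform +0.1 | 25% / 16% | +0.116 to +0.117 | +0.058 | +0.069 | +0.078 |
| Near threshold only | 10% / 5% | +0.012 to +0.016 | −0.021 | −0.010 | −0.003 |
| Near threshold only | 25% / 12–13% | +0.055 to +0.059 | −0.037 | −0.021 | −0.006 |

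The hand calculation and the simulation agree. Under a uniform benefit the loss runs from (0.104 − 0.091)/0.104 = 12.5% to (0.117 − 0.058)/0.117 = 50%. Non-walkers receive an average imputed speed of 0.65 to 0.75 m/s with arm alone in the model, and 0.33 to 0.62 m/s with a correlate.

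**Scale.** With SD 0.3 and 50 per arm, the standard error of a difference is about 0.3 × √(2/50) = 0.06 m/s. In the near-threshold rows each estimate lies within one standard error of zero. The largest gap between the two treatments of the data is 0.055 + 0.037 = 0.092 m/s, about 1.5 standard errors.

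**The case against.** The strongest reply is that the article never says inability is coded as missing. A recorded result of unable, a zero or a worst rank is compatible with every sentence quoted, and scoring rules of this kind are often left to a statistical analysis plan or full protocol that is not shown. This stands to the extent that nobody can say the trial *will* impute these values. It does not remove the point. The article fixes one imputation rule without exception, and that rule does not suit a timed test which its own entry criterion allows some participants to be unable to do.

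Further replies, and what remains of each:

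- *Needing help at entry is not inability at 3 or 6 months.* True. Many may recover, and the share unable is unknown.
- *The two-minute walk has a natural zero.* True. Its wording asks how far the person can go, so gait speed is the more exposed outcome.
- *A Mann–Whitney test is already planned.* It handles zeros or worst ranks well, but only if inability has been entered as a value.
- *The Shah-modified Barthel Index records ambulation.* True, and it could serve as a correlate in the imputation model, which shrinks the bias. The table shows that a correlate of 0.8 does not remove it. Table 1 of the article lists no baseline walking test.
- *Death.* A reader might infer that quality-of-life scores will be imputed after death and that QALYs will be materially overstated. The article does not say so. It gives no death rate, and it excludes people expected to live less than three months.

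**Conclusion.** The point holds as a gap between the entry criterion, the test conditions and the blanket imputation rule. As written, a participant still unable to walk unassisted could be assigned a walker's gait speed. If the share unable differs by arm, the estimated effect on gait speed, and less probably on two-minute walk distance, would be biased.

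Dilution is the usual result: about 12% to 50% of a uniform 0.1 m/s benefit in the scenarios tried. A reader might infer that imputation reverses the treatment effect. The calculations do not support that as a general statement. On average the sign changed only when the benefit was confined to people near the walking threshold, under assumed unequal rates of inability, and the reversed values (−0.003 to −0.037 m/s) are small against a standard error of about 0.06. With equal shares and no effect there is no bias.

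Two of seven secondary outcomes are concerned. The primary outcome and the sample size are not affected. The direction of the argument rests on the text; every magnitude rests on assumed rates, speeds and SDs.

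**What to change.** In the two test descriptions, state that inability to walk unassisted is recorded as a result, separately from a test that was not done for other reasons. Score it 0 m/s and 0 m, or give it the worst rank. In the analysis section:

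- include these scores in the intention-to-treat comparison, using the planned rank-based test or a robust method if zeros are frequent;
- report the number unable to walk unassisted in each arm at 3 and 6 months;
- limit multiple imputation to values that exist but were not collected.

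As a minor addition, with no size claimed, state that utility is set to 0 from the date of death when QALYs are calculated.

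The cost is one extra box on the assessment form and a few sentences of analysis text, best settled before any unblinded analysis. The small downside is a cluster of zeros that makes the distributions less normal.

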### 2-minute walk distance

In addition to the gait speed, the distance a person can walk and the amount of daily walking that a person is able and willing to do are strong indicators of his or her health and condition [21]. Hence, the two-minute walk test will also be conducted. Individuals walk at their usual speed as far as they can without assistance for 2 min and the distance is measured. Assistive devices can be used but would be kept consistent and will be documented from test to test.

### Functional status

Shah-modified BI will be used to assess and compare the improvements in the performance of ADL between the intervention and control groups. The Shah-modified BI is considered to be a valid measurement of ADL, as it is an empirically derived scale with proven inter-observer and test-retest reliability and validity which measures the patient’s functional ability [25]. It involves the assessment of 10-items, which include personal hygiene, bathing self, feeding, toilet, stair climbing, dressing, bowel control, bladder control, ambulation, wheelchair ambulation and chair/bed transfer. Five response options with their score are provided for each item and a total score will be calculated. The score can range from zero to 100 and the higher the score, the more independent the subject is.

### Balance confidence

The 16-items Activities-Specific Balance (ABC) Scale will be used to assess self-perceived efficacy in maintaining balance while performing a number of activities common in community-dwelling older adults such as bending, reaching, and walking both inside and outside the home [26]. This measure has good reliability and internal consistency. Participants have to indicate their level of confidence in doing the activity without losing their balance or becoming unsteady from choosing one of the percentage points on the scale with 0 % representing no confidence and 100 % representing complete confidence. The total rating is calculated and divided by 16 to obtain the overall ABC score. Based on the score, participants can be classified into three categories: < 50 % representing low level of physical functioning, 50-80 % representing moderate level of physical functioning and >80 % representing high level of functioning [26].

### Quality of life

We will use the Euro-QOL (EQ-5D) to measure patients’ quality of life. The EQ-5D is a standardized health-related quality of life questionnaire applicable to a wide range of health conditions and treatments, and it provides a simple descriptive profile and a single index value for health status which can be used in the clinical and economic evaluation of health care [27]. It is designed for self-completion by respondents. It consists of 16-items which measure health state on five dimensions: mobility, self-care, usual activities, pain/discomfort, and anxiety/depression. Each dimension comprises of three levels with their score: no problem = 1, some problem = 2, extreme problem = 3. The result is represented in a 5-digit number, in which each digit shows the level of the respective dimension [27]. Participants will also be asked about their health status and to indicate a value between 0 to 100 where 0 represents the worst health imagined and 100 represented the best health imagined [27]. The EQ-5D will also be administered at baseline for both intervention and control groups in order to calculate change in health-related quality of life before and after the trial which is needed for cost-effectiveness analysis.

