**Methods/design:**

This is a single blind (evaluator blinded), parallel, two-arm randomised controlled trial study design involving 100 recent stroke patients. The inclusion criteria are age ≥40 years, having caregiver support and recent stroke defined as stroke diagnosis within 4 weeks. Consenting participants will be randomized with varying block size of 4 or 6 assuming a 1:1 treatment allocation with the participating centre as the stratification factor. The baseline assessment will be done within 4 weeks of stroke onset, followed by follow-up assessments at 3 and 6 months. The tele-rehabilitation intervention lasts for 3 months and includes exercise 5-days-a-week using an iPad-based system that allows recording of daily exercise with video and sensor data and weekly video-conferencing with tele-therapists after data review. Those allocated to the control group will receive usual care. The primary outcome measure is improvement in life task’s social activity participation at three months as measured by the disability component of the Jette Late Life Functional and Disability Instrument (LLFDI). Secondary outcome variables consist of gait speed (Timed 5-Meter Walk Test) and endurance (Two-Minute Walk test), performance of basic activities of daily living (Shah-modified Barthel Index), balance confidence (Activities-Specific Balance Confidence Scale), patient self-reported health-related quality-of-life [Euro-QOL (EQ-5D)], health service utilization (Singapore Stroke Study Health Service Utilization Form) and caregiver reported stress (Zarit Caregiver Burden Inventory).

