Given the current heterogeneity and room for improvements in solutions related to post-stroke rehabilitation, there is a need for well-designed intervention and rigorous trial to close the gap. The Singapore Tele-technology Aided Rehabilitation in Stroke (STARS) Study is a parallel, two-arm (intervention-control), single blind (evaluator-blind) randomised controlled trial to determine if a novel tele-rehabilitation intervention can improve functional recovery of post-stroke patients. For the tele-rehabilitation intervention arm of this study, the team developed small affordable lightweight wireless wearable sensors which can be strapped onto patients to allow real-time biofeedback and collection of sensor data from the sensors for subsequent transmission to patient’s rehabilitation team wirelessly via the internet. The sensor data is automatically summarized in chart form for quick review by therapist to allow them to prescribe further rehabilitation exercises remotely. The system also automatically allows the patient to self-record videos of them exercising which will also be transmitted to the therapist (termed ‘tele-therapist’) for review where needed, and allow patients and their therapists to communicate with each other using video-conferencing. The study’s primary hypothesis is that this novel tele-rehabilitation intervention during the first three months after stroke admission will result in greater functional recovery compared to usual care three months after stroke admission, as determined by the Jette Late Life Functional and Disability Instrument (LLFDI). Secondary hypotheses are that tele-rehabilitation intervention during the first three months after stroke admission will result in greater functional recovery as determined by gait speed, 2-min walk test and Shah modified Barthel Index, less health service utilization, greater contact time with therapist, better balance, better quality of life, less caregiver burden and be more cost-effective compared to usual care three months after stroke admission. Process measures in the form of a diary will be used to assess improved adherence in rehabilitation. Outcomes will also be assessed again at six months post-stroke to determine whether any improvement in outcomes is sustained in both groups.

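### The stated EQ-5D input for cost-effectiveness, a before-and-after change, does not match the planned QALYs; an area under the curve regressed on baseline EQ-5D would reconcile them and gain precision

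*Protocol article*

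**What the plan says.** Two sections of the protocol article describe what EQ-5D contributes to the economic analysis.

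- **Quality of life.** EQ-5D is also given at baseline in both groups "in order to calculate change in health-related quality of life before and after the trial which is needed for cost-effectiveness analysis". This is the only use of the baseline value that the article states.
- **Cost-effectiveness.** "Quality adjusted life years (QALYs) will be computed for each individual using the EQ-5D score". These are set against "measures of health service utilization and cost over the study period". For the interval around the ICER, "a non-parametric bootstrapping method with 1000 replications of the data will be performed". No covariate is mentioned.

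Three other places bear on timing and adjustment.

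- **Abstract, Methods/design.** The baseline assessment is "followed by follow-up assessments at 3 and 6 months", and "The tele-rehabilitation intervention lasts for 3 months".
- **Background.** The secondary hypotheses, cost-effectiveness among them, are set at three months after the stroke admission. The same paragraph adds: "Outcomes will also be assessed again at six months post-stroke to determine whether any improvement in outcomes is sustained in both groups".
- **Analysis for outcome measures.** "Confounders are age, gender, ethnicity and marital status". Baseline EQ-5D is not among them.

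**The concern.** The two sections name different effect measures for one ICER. A change is a difference in utility between two visits. A QALY is utility accumulated over time, and with visits at 0, 3 and 6 months it can use all three values. An analyst who follows the Quality of life section and one who follows the Cost-effectiveness section could report different incremental effects from the same data.

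The end point of the change is also open: the hypothesis points to 3 months, while the study period and the last visit point to 6.

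This matters because treatment stops halfway through follow-up and the trial itself asks whether benefit lasts. A gain present at 3 months and reduced or gone at 6 is therefore a foreseen result, and it is where the readings diverge most.

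The second issue is how the baseline value is used. The stated use is subtraction. When the correlation between visits is below 1, subtraction over-corrects. Using no baseline value leaves chance imbalance in the estimate as extra variance. Regression on baseline avoids both.

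**Working it through.** The article gives no EQ-5D SD, visit correlation, effect or QALY figure, so there is no figure of the plan's own to reproduce. From the article: visits at 0, 3 and 6 months, treatment for 3 months, and 50 per arm (Sample size). Everything else below is an assumption.

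**1. Area against change.** The trapezoid area over 6 months, in years, is

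Q = 0.125·u0 + 0.25·u3 + 0.125·u6.

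Take an assumed gain of 0.05 in utility at 3 months.

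| Pattern | Area under the curve | Change from 0 to 6 months | That change × 0.5 year |
|---|---|---|---|
| Gone by 6 months | 0.25 × 0.05 = 0.0125 QALY | 0 | 0 |
| Sustained at 6 months | 0.375 × 0.05 = 0.0188 QALY | 0.05 | 0.025 |

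The baseline-to-6-month change misses a faded gain. If scaled to half a year, it overstates a sustained one. A baseline-to-3-month change would register the 0.05 in full but say nothing about the second half of the study period.

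**2. Precision from regression on baseline.** Assume a common SD s and equal correlation r between visits.

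- Var(Q) = s²[0.09375(1 − r) + 0.25r]
- Cov(Q, u0) = s²[0.125 + 0.375r]
- R² = [0.125 + 0.375r]² / [0.09375(1 − r) + 0.25r]
- SE ratio, adjusted to unadjusted = √(1 − R²)

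| r | R² | SE ratio | Reduction in SE |
|---|---|---|---|
| 0.3 | 0.2375² / 0.140625 = 0.401 | 0.774 | 23% |
| 0.5 | 0.3125² / 0.171875 = 0.568 | 0.657 | 34% |
| 0.7 | 0.3875² / 0.203125 = 0.739 | 0.511 | 49% |

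s cancels, so the percentages depend only on r and on the equal-correlation assumption.

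**3. Subtraction over-corrects.** Subtracting half a year of baseline utility gives weights −0.375, 0.25 and 0.125. The slope on baseline is −0.375 + 0.375r = −0.375(1 − r), which is negative for any r below 1. An arm that starts higher by chance is therefore marked down. The variance is 0.21875(1 − r)s². Against this version, regression lowers the SE by 1 − √(0.08422/0.15313) = 26% at r = 0.3, 1 − √(0.07422/0.10938) = 18% at r = 0.5, and 1 − √(0.05297/0.06563) = 10% at r = 0.7.

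**4. Illustrative scale.** With 50 per arm, an assumed SD of 0.20 to 0.30 and r of 0.4 to 0.6:

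- SE of the baseline difference = SD × √(2/50) = 0.040 to 0.060.
- A one-SE imbalance moves the unadjusted area by 0.275 × 0.040 = 0.011 to 0.35 × 0.060 = 0.021 QALY.
- It moves the baseline-subtracted area by 0.15 × 0.040 = 0.006 to 0.225 × 0.060 = 0.014 QALY in the opposite direction.
- The SE of the QALY difference is 0.016 to 0.026 unadjusted, 0.012 to 0.022 baseline-subtracted, and 0.010 to 0.017 with regression.

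**The case against.** The strongest case against is that the Quality of life sentence only explains why EQ-5D is also given at baseline. On that view the analysis itself is set under Cost-effectiveness, where QALYs are planned and a three-point area fits without strain. A journal article may also leave QALY construction and covariates to a fuller document. Much of this stands. Silence on area weights or on baseline regression would not by itself be a finding. What is left is a positive statement that a change is the input needed, which a fuller plan must either follow or contradict.

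A reader might go further in four ways that the document does not support.

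- **That the plan discards the 3-month value.** No section says so. The loss of a faded gain occurs only if the change is taken from baseline to 6 months. The 3-month cost-effectiveness hypothesis makes a change to 3 months an equally available reading.
- **That there is no correction for baseline.** A change score does correct, and in fact over-corrects. What is not described is regression adjustment. The listed confounders belong to the outcome regressions and do not show that baseline EQ-5D was ruled out of the economic analysis.
- **That imbalance biases the ICER.** Under randomisation, chance imbalance adds variance, and the planned bootstrap would carry it into the interval. The loss is one of precision.
- **That imbalance can be as large as the QALY effect.** This cannot be shown here, because SD, correlation and effect are all assumed.

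The lost gain and the imbalance left in an unadjusted area also belong to different analyses, so the two should not be added together.

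**Conclusion.** The point holds as an inconsistency in wording together with an improvement that costs nothing. The Quality of life and Cost-effectiveness sections name different quantities for the same analysis, and the article does not settle whether the change ends at 3 or 6 months. Under one literal reading, a transient benefit would be scored as zero; the QALY sentence does not require that reading.

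The firmest number is the precision gain over an unadjusted area, 23% to 49% for r of 0.3 to 0.7. It rests on equal correlation between the three visits and on a trapezoid area. Against a baseline-subtracted area the gain is smaller, 10% to 26% over the same range. The QALY shifts from imbalance are illustrative only. The primary outcome analysis is unaffected.

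**What to change.** Under Quality of life, replace the before-and-after change with a statement that baseline EQ-5D serves as the first point of the QALY and as a covariate. Under Cost-effectiveness:

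- define each participant's QALY as the area under the EQ-5D index at baseline, 3 and 6 months;
- estimate the between-arm QALY difference by regression on arm and baseline EQ-5D index;
- repeat that regression within each of the 1000 bootstrap replicates.

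State the horizon of the cost-effectiveness comparison once, so that the Background hypothesis and the study-period wording agree. With baseline in the model, it no longer matters to the between-arm estimate whether baseline utility is also subtracted, since the arm coefficient is the same either way.

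The cost is a change of analysis wording only. EQ-5D is already collected at baseline, and outcomes are already assessed at 3 and 6 months, so no new measurement is needed.
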